### Data collection and management

2.15

The demographic and baseline characteristic data will be collected by screeners when the participants are recruited. The relevant primary and secondary outcome will be measured by the outcome assessors at baseline, 6 weeks (mid-point of intervention), 11 weeks (end of intervention), and 19 weeks (after the 8-week follow-up period). Research assistants will conduct quality control of data collection and be responsible for data entry. The project manager will be responsible for initial data cleaning, identifying, coding, and converting into the proper format for data analysis.

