### Randomization and allocation concealment

2.8

Randomization will be performed at post-baseline assessment and stratified by age and sex. The random allocation sequence will be generated using the PLAN sentences of Statistic Package for Social Science 21.0 (SPSS 21.0) by an independent statistician who will be not involve in this trial. The eligible participants will be allocated to either *TCPSQ* group or unaltered lifestyle control group according to 1:1 equal proportion rule. To make sure that the risk of bias remains low, participants will be registered in the database by means of a participant ID code so that assessors are blinded during the analysis. The random allocation sequence will be managed by a specified project manager who is not involved in the recruitment program of this trail, and be concealed to the screeners and outcome assessors. Randomized group assignments were sealed in opaque white envelopes. Allocation concealment will be ensured, as the service will not release the randomization code until the participants are recruited into the trial after all baseline measurements are completed. Once participants consented to enter the trial, envelopes were opened and assignments made to *TCPSQ* group or control group. The eligible participants will be informed their allocation result by the project manager via telephone after post-baseline information assessment.

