### Blinding

2.10

In this trial, it is impossible to blind the participants and Qigong exercise coaches due to this being a nonpharmacological intervention trial. Nevertheless, 2 kinds of blind code will be used to blind the outcome assessors and statistician, and we will assign a specified project manager to be in charge of the management of the random allocation sequence and blind code of the participants’ allocation result will be replaced by using alphabet “A” or “B.” And the real meaning of “A” or “B” will be signed in the second blind code. A twice unclosed blind code will be performed in this trial. Firstly, after close of data-base, the project manager will deliver the group code “A” or “B” of participants to the statistician. Secondly, the project manager will declare the real meaning of group “A” or “B” after analysis of all data is completed. Furthermore, we will rule that each investigator has a well-defined obligation: the project manager and Qigong exercise coaches will not take part in the assessment of outcome; at the same time, the outcome assessors, laboratory technicians, data managers, and the statistic analyzer will be not involved in the participants’ screening and allocating. The allocation sequence and blind code will be preserved by an independent project manager who is irrelevant with the recruitment, intervention, assessment, and statistic analysis until the statistical analysis is completed.

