### Outcome assessment

2.13

Outcome measurements consist of basic characteristics of information, bioelectrical activity of cortical neurons, biomechanical balance of spinal column (dynamic and static), morphological balance of spinal column, degree of thoracic breathing and abdominal breathing, electrical activity of the heart, cardiopulmonary function, as well as self-reported symptom intensity, anxiety, depression, personality, self-esteem, quality of sleep, constitution in Chinese medicine, symptoms induced by spinal problems, and self-evaluation of Qigong training. The basic characteristics of information will be collected at baseline (1–2 weeks before randomized allocation). The relevant primary and secondary outcomes will be assessed at baseline, 6 weeks (at the mid-point of intervention), 11 weeks (at the end of intervention), and the physical and psychological self-reported scales measurement will be assessed at 19 weeks (after the 8-week follow-up period). Bioelectrical activity of cortical neurons, biomechanical balance of spinal column (dynamic and static), morphological balance of spinal column, degree of thoracic breathing and abdominal breathing, electrical activity of the heart, and cardiopulmonary function will be assessed at the Qigong and Human Science Laboratory of BUCM by experienced operators who are not otherwise involved in this study. Several outcome assessors who are incharge with the physical and psychological self-reported scales measurement will investigate the physical and psychological status of the participants (such as Symptom Checklist-90 [SCL-90],^[90]^ Self-Rating Anxiety Scale [SAS],^[91]^ Self-rating Depression Scale [SDS],^[92]^ Eysenck Personality Questionnaire-revised, Short Scale for Chinese [ EPQ-RSC],^[93,94]^ Rosenberg Self-esteem Scale [RSES],^[95]^ Pittsburgh Sleep Quality Index [PSQI],^[96]^ Constitution in Chinese Medicine Questionnaire [CCMQ],^[97]^ Self-made Questionnaires of Symptoms Induced by Spinal Problems (SQSSP), Self-made Qigong Training Self-evaluation Scale [SQTSS]) at college student activity center. A summary of all measures in the trial is shown in Table 1.

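### The project manager who holds the allocation sequence and blind codes is also assigned to clean and code the trial data, contrary to the protocol's aim of blinded data management

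*Protocol article*

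**What the plan says.** Four parts of the protocol article bear on this one role.

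- **Section 2.8 (Randomization and allocation concealment).** "The random allocation sequence will be managed by a specified project manager who is not involved in the recruitment program of this trail". The same section adds: "The eligible participants will be informed their allocation result by the project manager via telephone".
- **Section 2.10 (Blinding).** The project manager releases the blinding in two stages. First, "after close of data-base, the project manager will deliver the group code" A or B to the statistician. Then, when all analysis is finished, "the project manager will declare the real meaning of group" A or B. The section describes the role this way: "The allocation sequence and blind code will be preserved by an independent project manager who is irrelevant with the recruitment, intervention, assessment, and statistic analysis". It also separates duties for other staff: "the outcome assessors, laboratory technicians, data managers, and the statistic analyzer will be not involved in" screening or allocating participants.
- **Section 2.15 (Data collection and management).** Research assistants carry out quality control and data entry. After that, "The project manager will be responsible for initial data cleaning, identifying, coding, and converting into the proper format for data analysis".
- **Section 5 (Discussion), limitations paragraph.** The team undertakes to do all it can to keep assessors, laboratory technicians, data managers and statisticians from knowing who is in which group. This is offered as mitigation for unblinded participants and coaches.

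**The concern.** Cleaning and coding involve judgement. Someone decides which values to query, which to correct and how ambiguous entries are classified. When that person does not know the arm, errors of judgement should not favour either group. When the person does know it, they can, even without intent.

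The A/B scheme blinds the statistician to the groups but takes the file as it arrives. If a value was changed upstream by someone who knew the arm, analysing the file under neutral labels does not restore it. Participants and coaches cannot be blinded in this trial, so the protocol relies on blinding the people who measure, handle and analyse the data. Section 2.15 leaves a gap in the handling part of that chain.

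**Working it through.** No arithmetic applies. The check sets the duties given to one role beside the protections claimed.

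1. **Does the project manager know each participant's arm?** Yes. Section 2.8 gives the role the sequence and the telephone calls that disclose allocation. Section 2.10 gives it both the A/B assignment and the meaning of the letters, which it keeps until analysis is complete.
2. **Does the project manager handle the data?** Yes. Section 2.15 assigns initial cleaning, identifying, coding and conversion to that role by title, in the singular, as sections 2.8 and 2.10 do. No other section gives the work to anyone else.
3. **Is this data-management work?** Yes, by the heading of section 2.15 itself. The data managers named in section 2.10 are given no task in section 2.15, where entry goes to research assistants and cleaning to the project manager.
4. **Which statements conflict?** The Discussion wants those managing data to be unaware of allocation; section 2.15 gives the work to someone who is aware of it. Section 2.10 keeps data managers out of allocating; section 2.15 has their natural task done by the role that communicates allocation. Section 2.10 also calls the code-holder independent. Its list of separated functions does not name data management, so that statement is undercut rather than flatly contradicted.
5. **Do participant ID codes close the gap?** No. Section 2.8 uses IDs to blind assessors. They do not blind a person who holds the sequence and also does the identifying and coding.
6. **Which blinding claims survive?** Outcome assessors do not learn the arm through section 2.15. The statistician still works with A and B until analysis ends. The assessor and statistician blinding in the trial's design label is therefore not directly broken.
7. **When does cleaning happen?** Section 2.15 gives no time. Initial cleaning and conversion would ordinarily come before database close, but that is an inference.

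**The case against.** The best defence is that section 2.15 describes clerical preparation. Research assistants have already checked and entered the data, the word initial suggests a light first pass, and conversion to a suitable format need involve no judgement. Section 2.10 separates the project manager from four functions and data management is not among them. The Discussion's undertaking is a statement of effort, not a guarantee. Section 2.14 once uses the plural for project managers, so two people might share the title. The trial is a self-described pilot, and an article may leave detailed cleaning procedures to a fuller document.

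Much of this limits the point without removing it. The plural in section 2.14 does not assign cleaning to a second, blinded manager. A fuller document may add detail, but the article does more than omit detail: it states a role assignment that conflicts with its own aim.

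A reader might go further in three ways that the document does not support.

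- **That artefact, outlier and exclusion decisions for the EEG, respiration and ECG signals are made at this step.** No section says so. Section 2.13 has these measures taken by operators not otherwise involved in the study, and signal handling may sit with them.
- **That the A/B coding is worthless.** It still blinds the statistician's own choices under section 2.16, such as judgements of normality, transformations, and parametric or rank tests.
- **That the training self-evaluation scale unblinds assessors.** Section 2.13 ends its list of scales with the "Self-made Qigong Training Self-evaluation Scale [SQTSS]) at college student activity center". It does not say that controls receive the form, or that one assessor handles it together with the SCL-90, SAS and SDS. Table 1, which might settle this, is not available here. Those psychological scales are in any case completed by unblinded participants, a limitation the Discussion already admits. Having coaches collect the form would be no remedy, because section 2.10 bars coaches from outcome assessment.

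**Conclusion.** The role conflict is real and is stated in the text. The person who holds the sequence and codes and makes the allocation calls is also assigned to clean and code the data. This is at odds with the Discussion's aim for data managers and weakens the independence claimed in section 2.10.

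The size of any bias cannot be derived from the document, because it depends on how much discretion cleaning allows. If cleaning is purely clerical, the effect could be nil. If values are queried, corrected or recoded, every outcome passing through this step for up to 80 participants is exposed, and later blinding cannot undo it.

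The conclusion rests on two assumptions: that the title refers to the same person in sections 2.8, 2.10 and 2.15, and that cleaning leaves some room for judgement. This should be fixed, but it does not show that the trial's assessor or statistician blinding fails.

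**What to change.** - **Section 2.15.** Assign cleaning, coding, conversion and any exclusion decisions to the data managers already named in section 2.10. They should work by participant ID, without access to the sequence or either blind code, and finish before database close.
- **Section 2.10.** Limit the project manager to keeping the sequence, making the allocation calls and releasing the codes in two stages. Add data management to the functions from which that role is separate, and state that data managers are blinded, so that the section agrees with the Discussion.

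The cost is a reassignment among roles the protocol already names and a few lines of text. The change needs to be in place before data handling begins, because cleaning done with allocation known cannot be made blind afterwards.

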### Statistical analysis

2.16

Collected data will be recorded on standardized forms. Descriptive statistics will be calculated for dependent and independent variables. This analysis will include summary statistics of demographic information and outcome measures. Continuous variables will be summarized as mean (SD) ± standard deviation for normal distribution, and median (IQR) ± interquartile range for non-normal distribution. Normality will be tested using *Kolmogorov–Smirnov* test and categorical variables will be presented with frequencies or percentages. Appropriate transformations will be applied in cases of non-normal distribution. For the variables with a normal distribution, differences in terms of outcomes between groups will be compared using an independent *T-*test. If the variables have a non-normal distribution of ordinal level, statistical comparison between groups will be made by using the *Mann– Whitney U* test even after suitable transformations. Measures with a discrete distribution will be expressed as percentages and analyzed by the *X*^*2*^ or Fisher's exact test as appropriate. Subgroup analysis will be performed according to participants’ gender, personality, and constitution of TCM. Analysis of variance (ANOVA) will be used for the repeated measurement data, and *post-hoc* comparison between groups at different assessment time points will be conducted using multiple comparisons with adjustment to the type 1 error rate. Analysis of the primary and secondary outcomes will be on the basis of intention-to-treat (ITT) population and per-protocol (PP) population. The result of the ITT analysis will be compared with that of the PP analysis to check whether the results are consistent or not. If the statistical results of the ITT and PP population data are the same, the results will be deemed to be reliable; if they are contrary, we intend to adopt the results of the ITT population. The method of processing missing data will be the last observation carried forward (LOCF). This refers to assigning the last observed value of the end point indicator to the subsequent missing evaluation point; that is, the last observation response will be considered to be the study end point. Safety will be evaluated by tabulations of AEs, and will be presented with descriptive statistics for each group. A chi-square test or a Fisher's exact test will be used to compare the frequency difference in AEs between the 2 groups, and severe AEs will be listed in detail. To explore potential factors which might influence adherence, a logistic regression model and a linear mixed-effects model will be used and adjusted for potential confounders. Adherence-related data will be taken from training log records. All statistical tests will be implemented using IBM SPSS 21.0 with bilateral inspection. The level of statistical significance is assumed at 2-sided *P* value <.05.

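### A Kolmogorov-Smirnov test on the observed data chooses summary, scale and test, and the article does not say whether this rule or the repeated-measures ANOVA governs

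*Protocol article*

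**What the plan says.** All of the rule stands in section 2.16 (Statistical analysis) of the protocol article.

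- Gate: "Normality will be tested using *Kolmogorov–Smirnov* test and categorical variables will be presented with frequencies or percentages". The level, the use of the Lilliefors correction, and the unit tested (arm, visit, pooled data or residuals) are not given.
- Summary: "Continuous variables will be summarized as mean (SD) ± standard deviation for normal distribution", otherwise median and interquartile range.
- Scale: "Appropriate transformations will be applied in cases of non-normal distribution". No transformation is named for any outcome.
- Test if normal: "For the variables with a normal distribution, differences in terms of outcomes between groups will be compared using an independent *T-*test".
- Test if not normal, for variables described as ordinal: "statistical comparison between groups will be made by using the *Mann– Whitney U* test even after suitable transformations".
- Repeated data: "Analysis of variance (ANOVA) will be used for the repeated measurement data", followed by multiplicity-adjusted group comparisons at the assessment times.

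Section 2.13 has the outcomes measured at baseline, 6 and 11 weeks, with the self-reported scales measured again at 19 weeks. Section 2.3 describes a pilot meant to support the sample size of later trials, and the limitations in section 5 say effect sizes will be compared between groups for that purpose.

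**The concern.** Three choices that define the result are made from the outcome data: how it is summarised, on what scale, and by which test. A mean difference, a difference on a transformed scale and a rank comparison answer different questions and are not interchangeable inputs to a later sample-size calculation.

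A second problem is that every primary outcome is measured repeatedly. Each one therefore falls both under the t-test/Mann-Whitney rule and under the ANOVA sentence, and nothing ranks the two. Nor is it said what happens to repeated measurements that stay non-normal, or whether the transformation rule also applies to the ANOVA.

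At 30 to 40 per arm the gate also performs poorly as a decision tool. With the Lilliefors correction it is unstable for moderately skewed data; without it, such data are rarely flagged. The primary outcome list is long (EEG bands in two states, plantar-pressure, gait and spinal indices, symptom scales), so the gate would be used many times.

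**Working it through.** The plan gives no figure to reproduce. The check asks how often the gate would send the same outcome down different branches at different visits, if it is applied at each visit.

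**Inputs from the article.** 40 per group with 20% attrition (section 2.3), so 40 × (1 − 0.20) = 32 per arm.

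**Assumed inputs.** Gamma-distributed scores, the same true distribution at every visit, correlation 0.6 between visits, three visits, and a visit counted as non-normal if either arm rejects at 5%. Gamma skewness is 2/√shape, so shape 4 gives 2/√4 = 1.0.

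**Why the version of the test matters.** With mean and SD estimated from the data, the 5% critical distance is 0.159 (n = 30) and 0.139 (n = 40) with the Lilliefors correction. Without it, the values are 0.242 and 0.210.

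**Hand check.** If a visit is flagged with probability p and visits were independent, the chance of mixed branches over V visits is 1 − p^V − (1 − p)^V. Correlation between visits generally lowers this slightly.

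| Setting (32 per arm, skewness 1.0) | p per visit | Hand check | Simulated |
|---|---|---|---|
| Lilliefors, raw scale, 3 visits | 0.47 | 1 − 0.104 − 0.149 = 0.75 | 0.71-0.72 |
| Lilliefors, raw scale, 2 post-baseline visits | 0.47 | 2 × 0.47 × 0.53 = 0.50 | 0.49 |
| After square root: t-test v Mann-Whitney, 3 visits | 0.10 | 1 − 0.001 − 0.729 = 0.27 | 0.28-0.29 |
| After square root, then log: same, 3 visits | 0.03 | 1 − 0.000 − 0.913 = 0.09 | 0.09 |
| Uncorrected test, raw scale, 3 visits | 0.013 | 1 − 0.000 − 0.961 = 0.04 | 0.03-0.04 |

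The third and fourth rows follow the written order: transform first, and use Mann-Whitney only if non-normality remains. The choice of square root and log is an assumption, because the article names neither.

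**Sensitivity to the assumptions.** With four visits, 30 or 40 per arm and correlation 0.5 or 0.7, raw-scale Lilliefors flags are mixed as follows:

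- truly normal data: 31-34% (hand check: p = 1 − 0.95² = 0.0975, giving 1 − 0.95⁸ = 0.34)
- mild skew: 66-77%
- moderate skew: 76-85%
- strong skew: 44-72%

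The uncorrected test gives 0.1%, 1-8% (mild to moderate skew) and 16-42% (strong skew).

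**Type I error.** With no group effect and the raw-scale choice between t-test and Mann-Whitney, the two-stage rule rejects at about 0.05-0.06, against 0.045-0.06 for either test alone. If significance on either test were accepted, the rate is 0.06-0.07. The two tests disagree on significance in 2-4% of data sets.

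**The case against.** Five points can be made for the plan.

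1. A reader might infer that the plan switches methods from visit to visit. It does not say so. It speaks of variables, which can mean one choice per outcome, and the ANOVA sentence would give one method across visits if it were the main analysis. This stands as a limit on the point. What remains is that neither reading is fixed, and the transformation rule could still change the scale of the ANOVA.
2. A reader might take the 70% figure as the chance that an outcome is tested by different tests. It is not: it counts raw-scale flags only. The planned transformation step lowers mixing of t-test and Mann-Whitney to 9-29% under the assumed transformations. A switch between raw and transformed scale remains possible only if the transformation is chosen visit by visit.
3. A reader might infer that the P values are clearly wrong. The type I error results do not support that.
4. Section 2.10 gives the statistician only group codes A and B until the analysis is complete. This limits deliberate favouring of an arm. The choice still depends on the observed outcomes.
5. Naming scales and models is often left to an analysis plan that is not shown here. That would answer a complaint about silence. Here, however, the article itself states the data-dependent rule, and it is the rule that needs changing.

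**Conclusion.** The point holds in limited form. Section 2.16 fixes a rule under which the observed distribution decides the summary, an unnamed transformation and the between-group test, and it sets repeated-measures ANOVA beside that rule without an order of precedence. The effect measure can therefore shift between outcomes, and between visits if the gate is applied per visit.

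The size of any shift between visits cannot be read from the article. It depends on the version of the test, the skewness, the correlation, the number of visits and the transformations. At 32 per arm, skewness 1.0, correlation 0.6 and three visits, it runs from about 4% (uncorrected test) through 9-29% (t-test against Mann-Whitney after transformation) to about 70% (raw-scale Lilliefors flags). The harm is an unclear main analysis and effect sizes that may not be comparable, in a pilot meant to pass effect sizes on. It is not a material loss of type I error control.

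**What to change.** Remove the normality test as a decision rule. Before the data are seen, name one scale for each outcome; a log scale for EEG power and the raw scale for questionnaire totals are examples only. Make one baseline-adjusted repeated-measures model the main analysis of each outcome at all its visits, and report the group difference with a 95% confidence interval. Keep the rank-based or a bootstrap analysis as a stated sensitivity analysis, with residual plots as a check and not as a switch.

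With scale and method fixed, mixed methods across visits cannot occur. The sample size does not change, and the cost is wording, with somewhat less analysis work. The downside is a small loss of efficiency if an outcome proves very skewed on its named scale. This is a cheap improvement.

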### Sample size

2.3

There are no previous clinical trials to explore the beneficial effect of *TCPSQ* on college students from the integrating with physical fitness and psychological well-being. Therefore, this study is designed as a pilot study to calculate the appropriate sample size for future randomized clinical trials. Each group should include 30 participants, which is the minimum sample size for evaluating the effect of *TCPSQ*. Considering a 20% attrition rate, a total of 80 participants are necessary, with 40 participants in each group.

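### The between-group comparison is planned without adjustment for the baseline outcome value or the stratification factors, which gives up precision that the collected data could supply at no cost

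*Protocol article*

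**What the plan says.** Section 2.16 (Statistical analysis) fixes the treatment comparison. For normally distributed variables, "differences in terms of outcomes between groups will be compared using an independent" t-test; where normality fails even after transformation, Mann-Whitney U replaces it. Normality is judged by a Kolmogorov-Smirnov test. For longitudinal data, "Analysis of variance (ANOVA) will be used for the repeated measurement data", followed by post-hoc group comparisons at the assessment times with type 1 error adjustment. No covariate is named for any of these.

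Adjustment does appear in the same section, but only for factors that may influence adherence: "a logistic regression model and a linear mixed-effects model will be used and adjusted for potential confounders".

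Section 2.13 (Outcome assessment) supplies the baseline data: "The relevant primary and secondary outcomes will be assessed at baseline, 6 weeks", and then at 11 weeks, with the self-reported scales also at 19 weeks. Section 2.15 repeats that outcomes are measured at baseline. Section 2.8 sets the design: "Randomization will be performed at post-baseline assessment and stratified by age and sex", with allocation "according to 1:1 equal proportion rule".

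On numbers, section 2.3 states "Each group should include 30 participants" and "Considering a 20% attrition rate, a total of 80 participants are necessary, with 40 participants in each group". Section 2.16 plans intention-to-treat and per-protocol analyses, with last observation carried forward.

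**The concern.** With 40 or fewer students per arm, precision is scarce. A baseline value of the same measure is usually the strongest available predictor of the follow-up value, and it will already have been collected. An unadjusted comparison leaves the variation that it explains in the error term.

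It also leaves part of any chance difference at baseline in the reported effect. A follow-up-score comparison carries r times the imbalance, and a change-score comparison carries (r - 1) times it. ANCOVA removes this linear carry-over.

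Stratifying by age and sex and then leaving both out means that the analysis does not match the design. Standard errors are then, on average, slightly too large.

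The pilot's stated purpose makes this relevant. Section 2.3 says that the trial is to inform future sample sizes, and the Discussion intends to compare effect sizes between groups. Avoidable noise in those estimates passes into the next trial's planning. Because the article names these tests itself, this is a choice that it makes and not a detail left open.

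**Working it through.** **Numbers analysed.** Inflating 30 per group for 20% loss gives 30 / (1 - 0.20) = 37.5, so 38 per group and 76 in total. The stated 40 per group and 80 in total is a generous rounding up. In reverse, 40 x 0.80 = 32 remain per arm. The 30 has no stated derivation, so there is no planned power to reproduce. I use 32 per arm (after the stated attrition) and 40 per arm (intention-to-treat with carried-forward values). The point does not depend on this choice.

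**Assumptions.** The article gives no SD, effect size or correlation. I take a two-sided 5% level (section 2.16), an effect of 0.5 SD (assumed), equal SDs at baseline and follow-up, and r from 0.3 to 0.7 (assumed). The few degrees of freedom spent on covariates are ignored.

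**Formulas.** With follow-up SD = 1, the relative variance of the group difference is:
- t-test on follow-up scores: 1
- t-test on change scores: 2(1 - r)
- ANCOVA on baseline: 1 - r²
- ANCOVA against change scores: (1 - r²) / [2(1 - r)] = (1 + r) / 2

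Power is that of a two-sample t-test with standardised effect 0.5 / sqrt(relative variance).

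**Against a t-test on follow-up scores:**

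| r | ANCOVA variance | Power, 32 per arm | Power, 40 per arm |
|---|---|---|---|
| unadjusted | 1 | 50% | 60% |
| 0.3 | 0.91 | 54% | 64% |
| 0.5 | 0.75 | 62% | 72% |
| 0.6 | 0.64 | 69% | 79% |
| 0.7 | 0.51 | 79% | 87% |

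With 32 per arm, the effect detectable at 80% power is 0.711 SD unadjusted. Multiplying by sqrt(1 - r²) gives 0.62, 0.57 and 0.51 SD at r = 0.5, 0.6 and 0.7.

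**Against a t-test on change scores.** The variance ratio (1 + r) / 2 is 0.75, 0.80 and 0.85 at r = 0.5, 0.6 and 0.7. At r = 0.7 with 32 per arm, the change-score test has relative variance 2(1 - 0.7) = 0.6 and power 72%; ANCOVA has 79%. At r below 0.5, change scores do worse than follow-up scores.

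**Chance imbalance.** The baseline difference between arms has SD sqrt(2/40) = 0.224 SD units. The chance that it exceeds 0.3 SD in either direction is P(|Z| > 0.3 / 0.224 = 1.34) = 18%. At r = 0.5, an imbalance of 0.3 SD shifts a follow-up-score comparison by 0.5 x 0.3 = 0.15 SD, and a change-score comparison by 0.15 SD the other way.

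**Age and sex.** If together they explain an assumed 2 to 10% of outcome variance, adjusting for them lowers the variance by 2 to 10%.

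**The case against.** The strongest reply is that nothing here is invalid. Under randomisation the unadjusted test is unbiased over repetitions, and omitting strata tends to make it conservative. That stands, so the point is one of efficiency. The size also rests on an unknown correlation: at r = 0.3 only 9% of the variance is saved. That stands too. Stratification already limits imbalance in age and sex, and first- and second-year students aged 18 to 25 are a narrow group, so those two covariates add little.

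Some stronger readings are tempting, but the article does not support them:

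- **The ANOVA dilutes the effect.** A reader might infer that a group main effect averaged over baseline and later visits captures only two thirds (three visits) or three quarters (four visits) of a constant effect. The article never says that the main effect is the test of interest. A group-by-time test would use baseline, and the planned post-hoc contrasts are at single time points, so they are not diluted, though they are still unadjusted.
- **Baseline is ignored altogether.** The hypothesis in section 2.1 speaks of greater improvement, and section 2.16 does not say whether follow-up values or changes are tested. Change scores are not excluded, and against them the gain is smaller when r is high.
- **Imbalance enters the result in full.** Only r times it, or (r - 1) times it, does.
- **The t-test and ANOVA are rivals for one hypothesis.** They may serve different data, and naming the primary test is commonly left to an analysis plan that is not shown.
- **Every outcome has a usable baseline.** This cannot be shown for the training self-evaluation scale, which rates states during and after training; Table 1 is not visible.

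The pilot label does not remove the point, because section 2.16 tests at P < .05 and the effect estimates are meant to inform later trials.

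**Conclusion.** The point holds as a recoverable loss of precision. Section 2.16 names between-group tests with no adjustment for baseline outcome or stratification factors, while sections 2.13 and 2.8 provide both.

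Over assumed r of 0.3 to 0.7 and an assumed 0.5 SD effect, adjustment adds 4 to 29 percentage points of power at 32 per arm, and 4 to 27 at 40 per arm, if the t-test is on follow-up scores. If it is on change scores, the gain at r = 0.7 and 32 per arm is 7 points. Most of this comes from the baseline outcome. Age and sex matter mainly for consistency with the design. The planned analysis should be improved, but it is not invalid or biased.

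**What to change.** For each continuous outcome with a baseline measurement, replace the unadjusted t-test as the main comparison by the week-11 between-group difference with 95% CI from ANCOVA. The week-11 contrast of a mixed model on post-baseline values would serve equally. Include the baseline value, age and sex as covariates. Do not let a normality pre-test choose the method; if residuals are clearly skewed, use a transformation or a bootstrap interval.

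The cost is analysis wording only. The covariates are already collected, SPSS 21 fits both models, and the article already plans a linear mixed-effects model for adherence.
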